	Life-threatening conditions		x		x	x	Register
	Outpatient services, admissions and inpatient days		x		x	x	Register
	Use of social services		x		x	x	Register
	Intervention-specific services and treatment			x			Care managers and psychiatrists

***MINI*** Mini International Neuropsychiatric Interview

### Training and inter-rater reliability

All assessors have received the necessary training in the relevant instruments and receive ongoing support and supervision. All assessors have participated in regular joint ratings for PSP and GAF, in order to ensure inter-rater reliability. All cases of discrepancy between the referral diagnosis and a diagnosis made at the inclusion interview via the MINI interview will be discussed with the psychiatrist and the referring GP.

### Power and sample size

We made two sample size calculations, one for the depression treatment outcome study and one for the detection of depression study to see how many people to include in the depression treatment outcome study with the embedded detection of depression study

#### Sample-size calculation for the depression treatment outcome study

The primary outcome is a change in the BDI-II summary score. Clinical relevant treatment response at group level is defined as a difference in the degree of depression by 4 points measured by the BDI-II [46, 47]. No surveys have been carried out in Denmark that can contribute to the estimation of the standard deviation (SD) for BDI-II. However, according to international surveys, the SD for BDI-II can be set at 11 [46, 48–50]. There is no knowledge of the size of the intra-class correlation (ICC) in a Danish context; however a review of ICCs in depression in primary care suggests that the ICC can be set at 0.04 [51].

The sample-size calculation for the depression study based on the aforementioned figures shows that 328 participants with depression should be included in order to be able to reject the null hypothesis in the depression study. According to the null hypothesis, participants in the intervention group and the control group improve similarly in terms of symptoms with a power of 0.8 and a significance level of 0.05.

#### Sample size calculation for the detection of depression study

On the basis of a study carried out by Michell et al. [13], the positive predictive value of standard detection is estimated to be 45%. A clinical meaningful and possible [52] increase in the number is estimated to be up to detection of 60%. With the detection of depression study embedded in the depression study, the sample size calculation shows that 480 individuals should be included in order to be able to reject the null hypothesis in the depression study. According to the null hypothesis, participants in the intervention group and the control group improve similarly in terms of symptoms, with a power of 0.8 and a significance level of 0.05.

#### Summary

In all, 480 individuals should be included in the Collabri treatment for depression outcome study with the embedded detection of depression study in order to reject the null hypothesis.

#### Secondary outcomes

The power for the secondary outcomes for depression is estimated to be over 0.8 for all analyses [53–55]. See Table 2.

**Table 2 Tab2:** Power calculation for the secondary outcomes

Secondary outcome	Mean difference (MD)	Standard deviation (SD) of the pooled mean	Type 1 error	Calculated power
BAI	4 (57)	12 (57)	5%	99%
GAF-F	5 (*)	10 (56)	5%	99%
SCL-90-R	23 (55)	50 (55)	5%	99%

*Abbreviations*: *MD* mean difference, *SD* standard deviation, *BAI* Beck Anxiety Inventory, *GAF-F* Global Assessment of Functioning, *SCL-90-R* Symptom Checklist-90-Revised. *The expected mean difference for GAF-F has been conservatively estimated to 5 points as this is considered clinically relevant

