## Methods

### Aim and design

The aim of the study is to test the null hypothesis that treatment according to the Collabri model (intervention group) and treatment as usual (control group) has the same effect on depression symptoms in people with depression in primary care and to test the null hypothesis that the performance of case-finding and standard detection of depression in primary care is the same. The treatment outcome study is a cluster-randomised, clinical superiority trial in 480 patients diagnosed with depression in general practice. The detection of depression study is a cluster-randomised trial within the Collabri study setting.

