#### Outcome measures in the treatment outcome study

The primary outcome for the treatment outcome study is self-reported degree of depression measured by the Beck Depression Inventory (BDI-II) [27] at 6 months. BDI-II is a 21-item multiple-choice questionnaire assessing degree of depression and changes in depression mode by measuring symptoms of depression during the last 14 days. Each item has four statements reflecting increase in symptom severity from scores 0 to 3. The total score ranges from 0 to 63.

Secondary outcomes for the treatment outcome study are self-reported degree of depression measured by the BDI-II [27] at 15 months, self-reported degree of anxiety measured by the Beck Anxiety Inventory (BAI) [28] at 6 months, functional impairment measured with the Global Assessment of Functioning (GAF-F, split version) [29] obtained through a semi-structured interview with a research assistant, and self-reported psychological stress measured with the Symptom Checklist (SCL-90-R) [30] at 6 and 15 months.

The BAI is a 21-item multiple-choice questionnaire assessing physiological anxiety symptoms. Each item has four statements scoring 0 to 3, reflecting increase in the degree to which the participant has been bothered with the symptom over the last week. The total score ranges from 0 to 63. The GAF-F measures the participants’ level of functioning over the past month on a continuous scale ranging from 0 to 100. The SCL-90-R is a multi-dimensional questionnaire assessing mental health problems and psychopathological symptoms on a continuous scale from the lowest functional level of 0 to the highest functional level of 100. It consists of 90 items, each item graded on a scale of 0–4, based on the extent to which the participant has experienced the symptom within the past week. The questionnaire measures nine primary dimensions of symptoms and can be summed in the global severity index (GSI), measuring overall psychological distress.

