### Feasibility

By including 48 GPs, the GPs must each include 10-11 people with depression in the depression treatment outcome study with the embedded detection of depression study over a 15-month period. This is possible as 12 months prevalence rates indicate that a GP with 1600 registered patients on average will see 140 patients with depression per year [2].

Eight full-time care managers and one and a half psychiatrists (one full-time and one part-time) are employed in the Collabri project. Each care manager has a maximum caseload of 100 participants per year. Thus, it is realistic in terms of the capacity of care managers to complete the intervention in 240 participants with depression.

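### Table 2 gives 99% power for the BAI, but its own inputs at 480 patients give about 95% without clustering and about 87–88% with it; the SCL-90-R scale also needs correcting.

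*Protocol article*

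**What the plan says.** Under Power and sample size, the Secondary outcomes paragraph makes a general statement: "The power for the secondary outcomes for depression is estimated to be over 0.8 for all analyses". Table 2 gives the inputs and results by row, the last entry being power in per cent:

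- BAI: "BAI 4 (57) 12 (57) 5% 99"
- GAF-F: "GAF-F 5 (*) 10 (56) 5% 99"
- SCL-90-R: "SCL-90-R 23 (55) 50 (55) 5% 99"

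The planned size is in the Summary paragraph: "In all, 480 individuals should be included in the Collabri treatment for depression outcome study". The Feasibility section implies equal arms, since care managers are expected "to complete the intervention in 240 participants with depression". It also gives 48 GPs with 10 to 11 patients each. The primary sample-size paragraph sets the ICC at 0.04, and Statistical analysis commits to mixed models that allow for the cluster randomisation.

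On the SCL-90-R, the section on outcome measures in the treatment outcome study places scores "on a continuous scale from the lowest functional level of 0 to the highest functional level of 100". It goes on to describe 90 items, each graded 0–4 by how far the symptom was experienced, and a global severity index of overall distress.

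**The concern.** Three rows with quite different standardised differences (4/12 = 0.33, 5/10 = 0.50, 23/50 = 0.46) all show the same 99%. The BAI row has the smallest ratio. It also has the same 4-point difference as the primary outcome with a larger SD (12 against 11), so at the same sample size its power must be lower than that of the BDI-II.

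The BAI at 6 months is a named secondary outcome. With a stated power of 99%, a non-significant result could be taken as close to proof that no 4-point effect exists, which the design does not support to that degree.

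The SCL-90-R row raises a different question: whether 23 and 50 can be on the scale that the article describes, and in which direction an improvement would run.

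**Working it through.** **Inputs.** N = 480, 240 per arm (Summary; Feasibility). BAI difference 4, SD 12, alpha 5% (Table 2; the SD is read as that of individual scores). ICC 0.04 (primary sample-size paragraph). Cluster size m = 10 to 11 (Feasibility). Sidedness is not stated. The null hypothesis in Aim and design is one of equality, that treatment "has the same effect on depression symptoms in people with depression in primary care", which suggests a two-sided test.

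**Step 1: recover the convention from the primary calculation.** For a difference of 4, SD 11, power 0.8 and two-sided 5%:

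n per arm = 2 × (1.960 + 0.842)² × 11² / 4² ≈ 119, so 238 in total.

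Design effect at m = 10.5: 1 + (10.5 − 1) × 0.04 = 1.38.

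238 × 1.38 = 328.4, which matches the stated 328. The primary calculation is thus consistent with a two-sided test and a design effect of about 1.38.

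**Step 2: BAI without clustering.**

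SE = 12 × √(4/480) = 1.095; 4/1.095 = 3.65; power = Φ(3.65 − 1.96) = Φ(1.69) = 95.5% (95.4% with the noncentral t).

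**Step 3: BAI with clustering.** SE = 12 × √(4 × DE/480), with DE = 1 + (m − 1) × ICC.

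| ICC | m | DE | Power |
|---|---|---|---|
| 0.04 | 10 | 1.36 | 87.9% |
| 0.04 | 10.5 | 1.38 | 87.5% |
| 0.04 | 11 | 1.40 | 87.0% |
| 0.01 | 10 | 1.09 | 93.8% |
| 0.05 | 11 | 1.50 | 84.7% |

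With a t reference on 46 degrees of freedom (48 clusters less 2), the first row becomes 86.5%.

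**Step 4: what 99% would need.** n per arm = 2 × (1.960 + 2.326)² × 12² / 4² ≈ 331, so about 662 patients without clustering, or 662 × 1.36 ≈ 900 with it.

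**Step 5: the other rows.** GAF-F gives 99.98% without clustering and 99.7% at DE 1.38. SCL-90-R gives 99.9% and 99.0%. Both agree with the printed 99%, so the power error is confined to the BAI row.

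**Step 6: SCL-90-R scale.** The largest possible SD on a 0–100 scale is 50, reached only if half the patients score 0 and half score 100. An SD of 50 is therefore the limiting case on the stated scale and not a plausible value. The item description gives a raw sum of 0 to 90 × 4 = 360, on which 23 and 50 are unremarkable. On that sum a higher score means more symptoms, the opposite of the stated direction. Power depends only on the ratio 23/50, so it does not change with rescaling.

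**The case against.** The strongest defence is that the general claim of power over 0.8 is true, and that nothing in the design depends on the 99%. Both parts stand. At 480 patients the BAI has about 87–88% on the protocol's ICC, and the trial's size is set by the BDI-II calculation and the detection study, not by Table 2.

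It can also be said that any clustered BAI figure is conditional. The ICC of 0.04 is given for depression and not for the BAI. Clusters are provider numbers that may hold several GPs, so there may be fewer and larger clusters than 48, which would lower power. Covariates in the mixed model could raise it: a baseline correlation of 0.7 would give about 99% even with clustering, but the article states no such correlation and Table 2 lists only a difference, an SD and alpha. These points widen the range around 88%. They do not restore 99% from the stated inputs, because the unclustered figure already falls short. A one-sided 5% test without clustering gives 97.8%, still not 99%, and does not fit the convention behind the 328. Entering a total as if it were the per-arm number gives about 99% (328 per arm: 99.0%), but the article does not show that this was done.

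A reader might infer that dropout takes the BAI below 0.8. The article gives no attrition rate, so this cannot be established. Under an assumed 20% loss (384 patients, m = 8, DE 1.28) power is still 82%; it takes an assumed loss nearer 30% (336 patients, m = 7, DE 1.24) to reach 78%.

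A reader might also infer that the SCL-90-R wording would reverse the interpretation of that outcome. The same section describes symptom items and a distress index, so the intended direction can be recovered.

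**Conclusion.** The 99% in the BAI row is wrong as written. On the row's inputs, 480 patients and a two-sided 5% test, power is about 95% ignoring clustering and about 87–88% with an ICC of 0.04 and 10 to 11 patients per GP. Carrying that ICC over to the BAI is an assumption; ICCs from 0.05 down to 0.01 give about 85% to 94%. The risk of missing a true 4-point effect is roughly one in eight, not one in a hundred. The sentence that power exceeds 0.8 holds at 480 and needs no change, and the GAF-F and SCL-90-R power figures reproduce.

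Secondarily, the SCL-90-R description contradicts itself on range and direction, and its 0–100 scale does not plausibly fit the SD in Table 2. That is a fault of description and not of power. That 23 and 50 are raw sums is an inference, since the article does not state their scoring.

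**What to change.** Recompute the BAI cell with the two-sided test and design effect that reproduce the primary 328; at an ICC of 0.04 this gives about 88%. State under Table 2 the N, ICC and cluster size used, and note that the ICC is borrowed from the depression calculation. If covariate adjustment was assumed, state the correlation.

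For the SCL-90-R, replace the 0–100 functioning description with the range and direction of the scoring actually used, and express the difference and SD on that scale. Sum or mean item score is the sponsor's choice. If 23 and 50 are raw sums, they equal 23/90 = 0.26 and 50/90 = 0.56 as mean item scores, with the same power.

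The cost is one table cell, one footnote and one sentence. No change to the sample size, outcomes or analysis is needed; the only loss is a less favourable stated power for the BAI.

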### Feasibility

By including 48 GPs, the GPs must each include 10-11 people with depression in the depression treatment outcome study with the embedded detection of depression study over a 15-month period. This is possible as 12 months prevalence rates indicate that a GP with 1600 registered patients on average will see 140 patients with depression per year [2].

Eight full-time care managers and one and a half psychiatrists (one full-time and one part-time) are employed in the Collabri project. Each care manager has a maximum caseload of 100 participants per year. Thus, it is realistic in terms of the capacity of care managers to complete the intervention in 240 participants with depression.

### Statistical analysis

The Collabri study will be conducted according to the statistical principle “intention-to-treat” [56], which means that once a person is included in the project, he or she stays in the study population and is followed, regardless of whether the person is later excluded. In the detection of depression study the positive predictive value will be calculated and compared for both groups. Subgroup analysis will be performed in patients with a medical comorbidity and a personality disorder.

Linear mixed-effects regression models will be used to compensate for the cluster randomisation and potential confounders. To account for repeated measures, multilevel regression models with random effects will be used, estimated using an unstructured covariance matrix if possible. If not possible, other covariance matrices such as independent, interchangeable, auto-regressive, and Toeplitz will be estimated, and the best-fitting structure selected based on Bayes’ information criterion. This makes it possible to take “missing at follow up” into account under the assumption of “missing at random” by including covariates that are associated with missing values at follow up. The analysis levels are by GP, patients, and time. This method introduces less bias than the method whereby the last observation is used instead of the missing values, and the method whereby only cases with complete follow-up information are eligible for the analysis.

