### Recruitment and randomisation

#### Cluster level

Recruitment of GPs ran from May 2014 to July 2015. GPs in the catchment areas of the Capital Region in Denmark were invited to join the study through letters with information about the project and dates for a total of four information meetings. Additionally, the GPs were recruited through articles in professional newsletters and forums. Information visits and telephone calls to GPs were made on request.

The randomisation was conducted by centralised random computer-generated allocation sequence, carried out externally by the Research Centre for Prevention and Health (RCPH) at practice level, where each cluster corresponds to a provider number consisting of one or more GPs. Cluster randomisation was chosen because of the risk of bias in the form of contamination if the randomisation was on an individual level. The GPs were randomised to give either treatment as usual or CC according to the Collabri model. In both the treatment as usual group and the CC group, the GPs were subsequently randomised according to detection method, which was either standard detection of depression or case-finding. In standard detection the GPs were asked to use the MDI [19] as often as they usually did. In case-finding the GPs were asked to systematically use the MDI as a screening tool if they suspected depression. See Fig. 1 for an illustration of the randomisation process.

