#### Outcome measures in the detection of depression study

The primary outcome for the detection of depression study is the positive predictive value of referral diagnosis in two randomised detection settings: case-finding and standard detection. In the standard detection group, based on results from the referral diagnosis performed by the GP and the MINI carried out by the research assistant, the positive predictive value of the GP’s diagnosis is calculated. In the case-finding group, based on results from the MDI and MINI, the positive predictive value of the diagnosis and the sensitivity, specificit, and negative predictive value of the diagnosis are calculated.

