The results of this trial will add to the knowledge of collaborative care for depression in a Scandinavian context. If the Collabri model is shown to be more effective than treatment as usual in general practice, the results can contribute to improving the care and treatment for patients with depression in general practice with benefits to both patients and society. The results of the detection of depression study add to the knowledge of detection of depression in primary care. If case-finding is shown to be superior to standard detection, it will be recommended as a detection method in future treatment according to the Collabri model.

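### The stated primary PPV comparison does not name treatment arm, the stratum within which detection method was randomised; adding it is a free improvement

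*Protocol article*

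**What the plan says.** Under Recruitment and randomisation, Cluster level, allocation has two steps. Practices were first allocated to Collabri or usual care. Then: "In both the treatment as usual group and the CC group, the GPs were subsequently randomised according to detection method". This gives four randomised cells, with treatment arm as the stratum of the detection trial.

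The detection study's primary outcome is "the positive predictive value of referral diagnosis in two randomised detection settings: case-finding and standard detection". The Statistical analysis section gives one sentence to its analysis: "In the detection of depression study the positive predictive value will be calculated and compared for both groups". It names neither a model nor treatment arm.

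The next paragraph of that section adds: "Linear mixed-effects regression models will be used to compensate for the cluster randomisation and potential confounders". It goes on to repeated measures, covariance structures, missing follow-up, and levels of GP, patient and time. It does not say whether any of this applies to PPV.

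The result feeds a decision. The Discussion says: "If case-finding is shown to be superior to standard detection, it will be recommended as a detection method in future treatment according to the Collabri".

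**The concern.** An analysis normally carries the factor within which units were randomised. Here the only sentence on the PPV comparison describes two groups. The model paragraph fits BDI-II over time better than a binary result obtained once, at the baseline interview.

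The omission matters only if PPV differs between Collabri and usual-care practices. The article gives no figure for this but makes it plausible. GPs are not blinded (Blinding). The Collabri model includes GP training and instruments for detection (The experimental intervention). Referral in that arm also leads to a care manager and psychiatric supervision.

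Two consequences would follow. An analysis that ignores arm counts the arm-to-arm spread in PPV as noise, although the randomisation has already balanced it. An analysis that weights by referral numbers could also be shifted if the mix of arms differed between the detection groups. PPV is the detection study's only primary outcome, so its precision bears directly on the recommendation.

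**Working it through.** **Inputs from the article.** The detection sample-size section says "the positive predictive value of standard detection is estimated to be 45"% and "increase in the number is estimated to be up to detection of 60"%, with power 0.8 and significance level 0.05 (taken as two-sided). The ICC of 0.04 is given for the treatment study and assumed here for PPV. The Feasibility section gives 48 GPs with 10–11 patients each.

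**Assumptions.** There are 48 clusters of 10, 12 per cell. The article counts GPs, and a cluster may hold several, so this is not its own figure. The arm difference in PPV, d, is not given and is varied from 0 to 20 points.

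**The plan's own figure.** The article states that "the sample size calculation shows that 480 individuals should be included". Comparing 0.45 with 0.60 without continuity correction needs 173 per group, 346 in total. The design effect is 1 + (m − 1) × 0.04.
- m = 10: 346 × 1.36 = 471
- m = 10.5: 346 × 1.38 = 477
- m = 10.67: 346 × 1.387 = 480

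So 480 is reproduced with clustering allowed for.

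**Standard error with and without arm.** The variance of a cluster's PPV in a cell with mean p is p(1 − p)/10 × 1.36. Let S be the sum of these over the four cells, whose means are 0.45 ± d/2 and 0.60 ± d/2.
- True variance of the difference, which the arm-adjusted analysis estimates: S/48.
- Variance estimated when arm is ignored: (S/2 + 2 × d²/4)/24, because each detection group now contains an arm spread of d²/4.

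Example, d = 0.10. The cell means are 0.40, 0.50, 0.55 and 0.65, so S = 0.136 × (0.24 + 0.25 + 0.2475 + 0.2275) = 0.13124. True SE = √(0.13124/48) = 0.0523. SE ignoring arm = √((0.06562 + 0.005)/24) = 0.0542. The ratio is 1.04.

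**Power and type I error.** These were simulated with beta-binomial clusters, 20,000 runs per setting. A cluster-level t-test (46 df) was compared with the same analysis plus treatment arm (45 df). Type I error was simulated at 0.525 in both detection groups.

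| Arm difference d | SE ratio, arm ignored / adjusted | Power, arm ignored | Power, arm included | Type I error, arm ignored |
|---|---|---|---|---|
| 0 | 1.00 | 79.2% | 79.2% | 5.1% |
| 5 points | 1.01 | 78.9% | 79.3% | 4.9% |
| 10 points | 1.04 | 77.8% | 79.9% | 4.0% |
| 15 points | 1.08 | 75.7% | 80.8% | 3.5% |
| 20 points | 1.15 | 72.3% | 81.0% | 2.4% |

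Type I error with arm included stays between 4.7% and 5.1%.

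A closed-form check at d = 0.15: S = 0.12954, true SE 0.0519, SE ignoring arm 0.0563. The unadjusted test rejects above 2.013 × 0.0563 = 0.1133, so power is Φ((0.15 − 0.1133)/0.0519) = Φ(0.71) = 76%, in line with the simulation.

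**Shift of a patient-weighted comparison.** Shift = d × (Collabri share of case-finding referrals − Collabri share of standard-detection referrals).
- Equal shares, even 65% and 65%: 0. With Collabri practices referring 14 patients each and usual-care practices 6, in both detection groups, a simulation (4,000 runs, d = 0.10) returned 0.149 against a true 0.15.
- Shares of 60% and 40%: 0.20 × d, which is 1, 2, 3 and 4 points at d = 5, 10, 15 and 20. A simulation at d = 10 points returned 0.170 against a true 0.15.

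**The case against.** The strongest reply is that the article is silent and does not actually plan to omit arm. Comparing the two detection groups is how any factorial margin is described, adjusted or not. The text mentions potential confounders, and a full protocol or analysis plan may name the stratum. This stands: nothing here shows that the final analysis will leave arm out. But the article does state a primary comparison, does not name the stratum in it, and describes its models for another kind of outcome. A clarification is therefore fair.

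A reader might infer that the pooled PPV difference is confounded by treatment arm. The documents do not support that. Randomising within arm makes detection method independent of arm at practice level. An arm difference in PPV, or in referral volume, produces no shift alone. It takes an arm difference in PPV together with a Collabri referral share that differs by detection method, and the article quantifies neither.

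A reader might also infer that the confidence interval will be too wide. That holds only if clustering is handled and PPV differs by arm. A plain comparison of two proportions would err the other way: its SE is about 0.045 against 0.052–0.054, with coverage of 89–91%. The article does not say that clustering will be ignored, and its 480 is reproduced only with a clustering design effect.

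The power loss and the shift also belong to different estimators, a test on cluster PPVs and a patient-weighted difference, so they should not be added. With equally weighted clusters and equal numbers per cell, an additive arm effect cancels from the estimate whatever the referral counts.

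Finally, the effect is small at modest arm differences. The 5-point power gap needs an arm difference of 15 points, as large as the planned detection effect. That stands and limits the weight of the point.

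**Conclusion.** The point holds as a free improvement. It is not evidence of a biased or invalid analysis. Detection method was randomised within treatment arm, and the stated PPV comparison does not name that stratum.

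If PPV differs by arm, a cluster-level comparison that ignores arm is mildly conservative: about 2 points less power at a 10-point difference, 5 at 15 and 9 at 20, with practically nothing lost at 0 to 5. A patient-weighted comparison could shift by 1 to 4 points, and only if the Collabri share of referrals also differs between detection groups to the extent of 60% against 40%.

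These sizes rest on 12 clusters of 10 per cell, an ICC of 0.04 carried over from the treatment study, and arm differences and referral shares that are assumed because the article gives none.

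**What to change.** In the Statistical analysis section, replace the sentence on the PPV comparison with one stating that the case-finding minus standard-detection difference in PPV is estimated by a cluster-adjusted analysis suited to a binary outcome (cluster-level or mixed model), with treatment arm as a fixed effect. Optionally, show PPV in each of the four randomised cells as description, since the recommendation concerns use within the Collabri model.

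The cost is one sentence and one model term, taking the cluster-level analysis from 46 to 45 degrees of freedom. No new data or patients are needed, and the sample size of 480 is unchanged. If PPV does not differ by arm, power is the same either way (79% in both).

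### Practices of one or more GPs were randomised, but the stated analysis levels, and apparently the design effect, use the GP; the provider number should be the top level

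*Protocol article*

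**What the plan says.** Under Recruitment and randomisation, Cluster level, the allocation was "carried out externally by the Research Centre for Prevention and Health (RCPH) at practice level", and the unit is defined: "where each cluster corresponds to a provider number consisting of one or more GPs". GPs who share a provider number were therefore allocated together.

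Under Statistical analysis, linear mixed models are to deal with the cluster randomisation, and the hierarchy is listed: "The analysis levels are by GP, patients, and time". No practice or provider-number level appears.

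The sample-size section for the treatment outcome study rests on "a difference in the degree of depression by 4 points measured by the BDI-II", on the statement that "the SD for BDI-II can be set at 11", and on a review which "suggests that the ICC can be set at 0.04". It gives no cluster size. The nearest figure is under Feasibility: "By including 48 GPs, the GPs must each include 10-11 people with depression". The article gives neither the number of practices nor the number of GPs per practice.

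**The concern.** In a cluster-randomised trial the standard error of the treatment contrast has to reflect variation between the units that were randomised. If two or three GPs under one provider number take part, their patients share an allocation and may share a list population, staff and referral habits. A model whose highest level is the individual GP treats those GPs as independent replicates. It then counts more independent units than were randomised, and its standard error is too small whenever outcomes are correlated between GPs of the same practice.

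The same substitution in the design effect would overstate power. The primary BDI-II test and the comparison of positive predictive value (PPV) could both be affected. The PPV comparison is the more exposed, because 480 was sized on it with nothing to spare.

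**Working it through.** **Inputs.** From the sample-size sections: BDI-II difference 4, SD 11, ICC 0.04, PPV 45% versus 60%, power 0.8, alpha 0.05, stated totals 328 and 480. From Feasibility: 48 GPs, 10–11 patients each, and 240 patients in the intervention arm, which implies 1:1 allocation. Two-sided testing is assumed.

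**Step 1: reproduce the stated totals.**
- BDI-II without clustering: n per arm = 2 × [11 × (1.96 + 0.84)/4]² = 118.7 (unrounded normal quantiles), so 119, or 238 in total.
- PPV without clustering (pooled-variance formula, no continuity correction): 173 per arm, or 346 in total.
- Design effect (DE) with m = 10.5: 1 + 9.5 × 0.04 = 1.38.
- 238 × 1.38 = 328, as stated. 346 × 1.38 = 477, against 480.
- Solving for m: 1 + (328/238 − 1)/0.04 = 10.45, and 1 + (480/346 − 1)/0.04 = 10.68.

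Both totals point to a cluster of 10–11 patients, which is the number per GP under Feasibility. The cluster size is inferred; the sample-size sections do not state it.

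**Step 2: clustering by practice.** Let g be the number of GPs per practice, each with 10 patients, and s the share of the 0.04 ICC that lies at practice level. The document gives neither. Both randomisations (treatment and detection method) are taken to be by provider number.

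- DE by GP: 1 + 9 × 0.04 = 1.36
- DE by practice: 1.36 + 10 × (g − 1) × 0.04 × s
- SE ratio, GP-level model to correct: √(1.36 / DE by practice)
- Type I error ≈ 2 × [1 − Φ(1.96 × SE ratio)]
- Power: normal approximation with 240/DE effective patients per arm

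| g | s | DE | SE ratio | Type I error | PPV power | BDI-II power |
|---|---|---|---|---|---|---|
| 1 | any | 1.36 | 1.00 | 5.0% | 81% | 93% |
| 1.2 | 0.5 | 1.40 | 0.99 | 5.3% | 80% | 92% |
| 1.2 | 1 | 1.44 | 0.97 | 5.7% | 79% | 91% |
| 2 | 0.5 | 1.56 | 0.93 | 6.7% | 75% | 89% |
| 2 | 1 | 1.76 | 0.88 | 8.5% | 70% | 85% |
| 3 | 0.5 | 1.76 | 0.88 | 8.5% | 70% | 85% |
| 3 | 1 | 2.16 | 0.79 | 12.0% | 61% | 77% |

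A simulation with 48 GPs, 10 patients each, and a GP-level comparison gives 7.0–8.8% at 2 GPs per practice and 8.4–11.7% at 3, in line with the table. A practice-level comparison stays at about 5%.

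**Limits of the approximation.**
- The 1.2 rows put the mean number of GPs into a formula for equal practices. If 80% of practices have one GP and 20% have two, 0.4/1.2 = one third of GPs share a practice. At s = 1 the DE is then 1.36 + 10 × 0.04/3 = 1.49 rather than 1.44, and type I error is about 6.1%.
- With a t reference on practices minus 2 degrees of freedom, BDI-II power at s = 1 is 82% at 2 GPs per practice and 71% at 3, rather than 85% and 77%.

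**The case against.** The strongest reply is that GP is simply this article's word for the cluster. The eligibility section headed Cluster level speaks of GPs holding a provider number. The randomisation section says practice level and then says that GPs were randomised. Patients are said to follow their GP's allocation. The mixed models are introduced precisely to handle the cluster randomisation. On that reading the GP level is the provider number, the 48 GPs are 48 practices, the design effect is right, and only the wording is loose. This stands as a possibility. It is not established: the article defines a cluster as possibly containing several GPs, so the two terms are not synonyms, and no sentence says that one is meant for the other.

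A second reply is that each practice may have had one participating GP, in which case nothing changes. This also stands as a possibility, but nothing limits participation to one GP per provider number.

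A third reply is that BDI-II has power to spare, because 480 exceeds 328. That is largely true of power. It does not protect the type I error, and the PPV comparison has no such reserve.

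Some details belong in an analysis plan that is not shown: the degrees-of-freedom method, and the choice between a logistic mixed model and GEE for the PPV comparison. Their absence here is not a fault. Nor does the article say that the PPV comparison ignores clustering.

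**Conclusion.** Read literally, the analysis levels omit the randomised unit, and both stated totals fit a per-GP cluster size. That inconsistency stands and should be corrected.

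A reader might go further and infer that the planned primary test has an inflated type I error, or that the trial is underpowered. The document does not support that. Harm requires three things together: that GP does not mean practice, that several GPs under one provider number recruit, and that outcomes correlate between GPs within a practice. None of the three is quantified.

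If all three hold, the effect runs from negligible (type I error 5.3–5.7%, PPV power 79–80% at a mean of 1.2 GPs per practice) to material (8–12% and 61–70% at 3). BDI-II power falls below 80% only at 3 GPs with the whole ICC at practice level, at 77%, by the normal approximation. These figures assume 10 patients per GP and a total ICC of 0.04, with half to all of it at practice level.

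**What to change.** In Statistical analysis, name the randomised provider number as the top-level random effect, with GP nested within it if wanted, then patient and time. State that the PPV comparison allows for clustering by the same unit. Give the number of practices randomised and the expected or actual patients per practice, and restate the design effect and both powers from them. If GP was meant as practice throughout, say so and give the practice count; the calculations then stand.

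The cost is small. Allocation was made by provider number, so no new data are needed. If multi-GP practices took part, intervals become slightly wider and the stated power somewhat lower. Recruitment ended on 31 December 2016, so the restated power serves interpretation and cannot change enrolment.
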